### 3.2. Economic Evaluation

An incremental cost–utility analysis (CUA) will be conducted alongside the feasibility study to generate exploratory cost data of BCI rehabilitation compared to standard care, acknowledging the limited precision afforded by the single-arm design. The economic evaluation will adopt a healthcare system perspective over a 24-week time horizon, consistent with the clinical follow-up period.

To keep the economic evaluation focused, it is organized around two scopes: (1) the within-trial 24-week cost–utility analysis from a healthcare-system perspective described above and (2) a secondary long-term extrapolation. For the latter, a cohort state-transition (Markov) model, structured around post-stroke functional health states (for example, FMA-UE severity together with functional dependency) and an absorbing death state, will project costs and quality-adjusted life years over 2-year and 5-year horizons, using an annual cycle with half-cycle correction and discounting at 3% per annum (0% and 5% in sensitivity analysis), consistent with Singapore health-technology-assessment norms. Transition probabilities and utilities will be derived from the trial, the TTSH registry, and the published literature; a societal perspective incorporating productivity losses and informal caregiver time will be explored as a sensitivity analysis rather than as a primary scope. As it remains uncertain whether clinical gains from BCI-rehabilitation are sustained into the chronic phase beyond the trial follow-up period, all estimates extrapolated beyond 24 weeks will be treated as exploratory and interpreted with caution. Structural and parameter uncertainty will be characterized through deterministic and probabilistic sensitivity analyses, reported in accordance with CHEERS 2022.

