### 3.3. Comparator Group: Historical Controls

Given the single-arm feasibility design, the comparator group will be derived from the TTSH stroke rehabilitation registry (2017–2025). Historical controls will be propensity-matched to BCI participants based on (1) baseline FMA-UE score, (2) age, (3) stroke type (hemorrhagic vs. ischemic), and (4) time post-stroke at rehabilitation admission (2–12 weeks). To reduce residual confounding, the propensity model will additionally include sex, baseline functional status (admission FIM and MBI), comorbidity burden (Charlson Comorbidity Index), clinically relevant concomitant medications (for example antispasticity and mood-active agents), the total inpatient rehabilitation therapy dose, and the calendar year (era) of admission. Historical control data will be obtained from an institutional inpatient stroke rehabilitation cohort assembled between 2022 and 2025 (more than 100 patients), for which baseline and discharge EQ-5D-5L utilities and FMA-UE scores are available to support propensity matching and quality-adjusted life year estimation. Corresponding inpatient rehabilitation cost data will be obtained from hospital administrative and costing databases. FMA-UE categories may use severe impairment (FMA-UE 0–19) and moderate-to-mild impairment (FMA-UE 20–47). This approach has been previously validated in the TTSH setting for evaluating upper extremity recovery outcomes [40]. Matching will be performed using nearest-neighbor propensity score matching with a caliper of 0.2 standard deviations to ensure adequate balance on baseline covariates. The matching ratio will be 1:3 (BCI/control) to maximize statistical power while maintaining adequate matching quality. Balance diagnostics will be assessed using standardized mean differences (target < 0.1 for all covariates) and variance ratios. To limit temporal confounding arising from the eight-year registry window (2017–2025)—over which ward staffing, rehabilitation protocols, and case-mix may have changed—the primary comparator analysis will be restricted to the contemporaneous 2022–2025 inpatient cohort, calendar year will be included as a matching and adjustment covariate, and models will additionally be fitted with admission era as a fixed effect; the influence of the matching window will be examined in sensitivity analyses that progressively restrict controls to narrower, more recent time bands. Sensitivity analyses will explore alternative matching specifications, including different caliper widths and matching algorithms (genetic matching, coarsened exact matching) to assess robustness of findings to matching choices. If precise stroke onset dates are unavailable for historical controls, hospital arrival date will be used as a proxy, consistent with Singapore Stroke Registry methodology.

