### 3.6. Effectiveness Measure

The primary effectiveness measure for the cost-utility analysis will be quality-adjusted life years (QALYs), calculated from EQ-5D-5L utility scores collected at baseline, week 3–4, week 12, and week 24. Singapore-specific value sets will be applied to convert EQ-5D-5L health states to utility weights [46]. QALYs will be calculated using the area-under-the-curve method with linear interpolation between assessment points. For historical controls, EQ-5D-5L data will be extracted from the TTSH registry where available; if unavailable, utility values will be mapped from functional outcomes (FMA-UE, Barthel Index) using validated mapping algorithms [47].

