### 3.7. Cost-Effectiveness Analysis

The incremental cost-effectiveness ratio (ICER) will be calculated as the difference in mean costs between BCI and standard care groups divided by the difference in mean QALYs: ICER = (Cost_BCI—Cost_Control)/(QALY_BCI—QALY_Control). Results will be interpreted against the Singapore willingness-to-pay threshold of approximately SGD 50,000–100,000 per QALY gained. A secondary cost-effectiveness analysis will calculate the cost per point improvement in FMA-UE to provide clinically interpretable metrics alongside the cost-utility analysis.

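### The 24-week QALY comparison needs control utilities that the primary control cohort is not described as having, and no adjustment for baseline utility is stated

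*Protocol article*

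**What the plan says.** All references are to the protocol article.

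- **Horizon.** Section 3.2: "The economic evaluation will adopt a healthcare system perspective over a 24-week time horizon, consistent with the clinical follow-up period".
- **QALYs.** Section 3.6 has them "calculated from EQ-5D-5L utility scores collected at baseline, week 3–4, week 12, and week 24", and adds: "QALYs will be calculated using the area-under-the-curve method with linear interpolation between assessment points". Control utilities come from the registry where they exist; otherwise they are mapped from FMA-UE or the Barthel Index.
- **Controls.** Section 3.3 says that "the primary comparator analysis will be restricted to the contemporaneous 2022–2025 inpatient cohort", a cohort of more than 100 patients "for which baseline and discharge EQ-5D-5L utilities and FMA-UE scores are available to support propensity matching" and QALY estimation. No later control utility, FMA-UE or Barthel score is described.
- **Matching.** Section 3.3 lists FMA-UE, age, stroke type, time since stroke, sex, admission FIM and MBI, comorbidity, medication, therapy dose and calendar year. EQ-5D-5L is not listed. The ratio is 1:3.
- **Estimator.** Section 3.7 defines the ICER as "the difference in mean costs between BCI and standard care groups divided by the difference in mean QALYs", read against SGD 50,000–100,000 per QALY. It mentions no adjustment for baseline utility.

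**The concern.** The stated horizon and the stated control data do not fit together. Section 3.6 needs a utility curve to week 24 in both groups, but the primary control cohort is described with two points, the second at discharge. Mapping needs functional scores at the missing times, and none is described for controls after discharge. The protocol gives no rule for control utility between discharge and week 24, so one group's late QALYs would be measured and the other's assumed.

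The Discussion accepts that substantial spontaneous recovery occurs 2–12 weeks after stroke. Depending on the rule chosen, some of that recovery could count for BCI and not for controls.

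Separately, a starting difference in utility feeds into the area under the curve. Baseline EQ-5D-5L could absorb it in both groups, yet the plan assigns it no role in matching or in estimating the difference.

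The planned safeguards do not cover this. Section 3.9 varies the mapping assumptions, not the valuation after discharge. Monte Carlo simulation describes parameter uncertainty and does not remove a structural mismatch. Section 3.10 lists four limitations, and unequal follow-up of utilities is not among them.

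**Working it through.** The protocol states no utility, QALY or ICER figure, so there is nothing to reproduce. I applied its own area-under-the-curve rule.

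**From the protocol:** utilities at weeks 0, 3–4 (taken as 4), 12 and 24; controls at baseline and discharge; 12 BCI participants and 1:3 matching, hence at most 36 controls; upper threshold SGD 100,000.

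**Assumed:** utility 0.40 at baseline and 0.55 at discharge; discharge at week 4 or 6; control discharge value carried forward; utility SD 0.15–0.30; incremental cost as stated below.

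**1. Weight of the late points.** In the BCI curve, week 12 carries (4 + 6)/24 = 42% and week 24 carries 6/24 = 25%. With discharge at week 4, 20/24 = 83% of the control period has no described measurement.

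**2. Spurious gain with zero true effect.** Both groups follow the same path and gain g12 and g24 over the discharge value by weeks 12 and 24.

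- Discharge at week 4: BCI minus control = (10·g12 + 6·g24)/52.
- Discharge at week 6 (week-4 utility 0.50 on the same line): (10·g12 + 6·g24 − 0.15)/52.

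| g12 / g24 | Discharge week 4 | Discharge week 6 |
|---|---|---|
| 0.02 / 0.03 | 0.0073 | 0.0044 |
| 0.05 / 0.08 | 0.0188 | 0.0160 |
| 0.10 / 0.15 | 0.0365 | 0.0337 |

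**3. Yardstick.** A true 0.05 benefit reached at week 4 and sustained: 0.5 × 0.05 × 4/52 + 0.05 × 20/52 = 0.0019 + 0.0192 = 0.0212 QALY.

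**4. Effect on the ICER.** Suppose a linear 0.10 rise in both groups from week 4 to week 24, with controls carried forward. The spurious part is 0.5 × 0.10 × 20/52 = 0.0192, for a total of 0.0404. At SGD 3,000 the ICER moves from 3,000/0.0212 ≈ 142,000 to 3,000/0.0404 ≈ 74,000. It crosses 100,000 only if the incremental cost lies between about SGD 2,120 and 4,040. At 2,000 both ICERs are below that line, and at 5,000 both are above.

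**5. Baseline utility.** The standard error of an unmatched standardized difference, 12 vs 36, is √(1/12 + 1/36) = 0.33. Times SD 0.15–0.30 this is 0.05–0.10 utility. If it persists, × 24/52 gives 0.023–0.046 QALY.

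**6. One rule in both groups.** With identical paths, measurement at week 4 in both and the same rule afterwards, the difference is 0. If controls are discharged at week 6 and BCI is valued from week 4, carrying both forward gives (0.45 × 4 + 0.50 × 20)/52 − (0.475 × 6 + 0.55 × 18)/52 = 0.2269 − 0.2452 = −0.018. Timing of discharge therefore matters and needs its own sensitivity analysis.

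**7. A baseline-to-discharge primary analysis.** It keeps 0.0019 of the 0.0212 QALY but all of the BCI cost: 3,000/0.0019 ≈ SGD 1.56 million per QALY (unrounded denominator).

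**The case against.** Much can be said for the plan. The analysis is secondary and labelled exploratory; confounding from historical controls and low precision are acknowledged; no feasibility benchmark or interim decision depends on it. These points stand and limit the severity.

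Several stronger readings are tempting but not supported:

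- **That baseline utility is ignored.** It is the first point of the curve, section 3.3 says it is available to support matching, and FMA-UE, FIM and MBI are matched and act as proxies. What holds is that EQ-5D-5L is not a listed covariate and no adjustment for it is stated. The proxies make the range in step 5 an upper one.
- **That later recovery is certain to be credited to BCI alone.** This requires carrying the discharge value forward, which the protocol does not say. Size and direction depend on the missing rule.
- **That control costs are inpatient only.** Section 3.3 names inpatient cost data without excluding others. Section 3.4 includes downstream use, section 3.5 draws on billing data, and Table 2 lists outpatient care and readmissions to 24 weeks for both groups.
- **That the ICER would cross the threshold.** It does so only within the cost band in step 4, and the protocol gives no incremental cost.

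One could also say that section 3.7 only defines an ICER and that regression details belong in an analysis plan. That is fair for model form. It does not resolve the conflict between a 24-week curve and a cohort described only to discharge.

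**Conclusion.** The concern holds in a limited form. As described, the primary control cohort cannot supply the week-12 and week-24 utilities that the 24-week QALY comparison uses, and mapping has no stated inputs to fill the gap. Under an assumed carry-forward rule the artefact is about 0.004–0.037 QALY, comparable with 0.021 for a true sustained 0.05 benefit. Leaving out baseline EQ-5D-5L exposes the difference to a further 0.023–0.046 QALY per standard error of imbalance. That is an upper range and is chance imprecision rather than systematic bias. All utility levels, gains, SDs and costs are assumptions.

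A reader might infer that the economic result is invalid or that the trial's main conclusions are at risk. The documents do not support that, because the analysis is secondary and exploratory. It should still be fixed: it is one of the four study aims, it is read against a willingness-to-pay threshold, and trial utilities feed the long-term model.

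**What to change.** In sections 3.3, 3.6, 3.7 and 3.9:

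1. Keep the 24-week horizon. Base the between-group QALY difference on one stated post-discharge valuation rule, applied identically to both groups from baseline and discharge (week 3–4 in BCI) utilities.
2. Add sensitivity analyses on post-discharge recovery and on differing length of stay. The protocol never says that control discharge coincides with week 3–4, and step 6 shows the effect of a mismatch.
3. Report measured BCI utilities at weeks 12 and 24 descriptively.
4. Present baseline to discharge over a common duration as a sensitivity analysis. It should not be primary, because it counts the full BCI cost against about one eleventh of the QALY gain (step 7).
5. Add baseline EQ-5D-5L to the propensity model and estimate the QALY difference by regression on baseline utility.

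If control utilities or mappable scores at weeks 12 and 24 do exist, section 3.3 should say so, and items 1 to 4 fall away.

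The cost is wording and some extra analysis, with no new data. The downside is that the between-group estimate no longer uses the measured late BCI utilities and rests on a stated extrapolation assumption.

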
### 3.4. Cost Data Collection

Costs will be estimated from the healthcare system perspective and will include both intervention costs and downstream healthcare resource utilization. All costs will be reported in 2025 Singapore dollars (SGD) (Table 2).

### 3.5. Cost Perspective and Therapy Time Differential

The BCI intervention is modeled as additional adjunctive therapy in addition to standard of care rather than a substitute for standard care. Under this assumption (Scenario A), BCI participants receive 30 min of BCI training plus 60 min of standard occupational therapy per session (90 min total), whereas standard care patients receive approximately 60 min of occupational therapy per session based on TTSH rehabilitation protocols [40]. The incremental cost of BCI therefore includes both equipment-related costs and the additional 30 min of therapist time per session. Where available, actual billed charges from hospital administrative databases will be used to estimate healthcare costs. For intervention-specific costs not captured in routine billing (e.g., BCI equipment depreciation, additional therapist time), unit costs will be derived from institutional costing data. This pragmatic approach balances data availability with accuracy of cost estimation. A sensitivity scenario modeling partial substitution—approximately 25%, rather than 50%, of within-session supervision withdrawn from the midpoint of the training course following an initial supervised orientation period, noting this proportion may vary in practice—will be examined to explore conditions under which a favorable ICER may be achievable.

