**Healthcare Utilization Costs (Both Groups)**	
Inpatient rehabilitation	Length of stay, ward type (Class B2/C subsidized wards as reference case), average daily bed cost, total OT/PT sessions
Outpatient services	Rehabilitation clinic visits, community therapy sessions (post-discharge)
Readmissions	Any stroke-related or rehabilitation-related hospital readmissions within 24 weeks

**Table 3 jcm-15-05692-t003:** RE-AIM framework assessment domains and variables.

Domain	Variables to Be Collected
Reach	Percentage excluded by eligibility criteria; proportion of eligible patients who participate; characteristics of participants versus non-participants
Effectiveness	Primary outcome measures (FMA-UE, ARAT); quality of life outcomes; adverse events; subgroup analyses; cost-effectiveness metrics
Adoption	Setting exclusion rates; patient disposition; staff participation rates; characteristics of participating versus non-participating staff
Implementation	Protocol adherence and fidelity rates; adaptations made during study; time and resource costs; consistency across staff and settings
Maintenance	Long-term primary outcomes (6+ months); sustained subgroup effects; organizational adoption sustainability

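### Routine care in both groups is priced at billed charges and the BCI add-on at institutional cost, so the ICER is distorted, in an unknown direction, whenever routine use differs between groups

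*Protocol article*

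**What the plan says.** Section 3.5 of the protocol article sets an order of price sources. For healthcare costs in general, "Where available, actual billed charges from hospital administrative databases will be used to estimate healthcare costs". For intervention-specific items that routine billing does not capture, with equipment depreciation and additional therapist time as examples, "unit costs will be derived from institutional costing data". The section calls this a pragmatic balance between data availability and accuracy.

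Section 3.4 fixes the viewpoint: "Costs will be estimated from the healthcare system perspective and will include both intervention costs and downstream healthcare resource utilization". It also sets 2025 Singapore dollars as the currency. Table 2 lists the BCI items for the intervention group only. It lists routine utilization (inpatient stay, outpatient services, readmissions) for both groups, and describes the inpatient item as "Length of stay, ward type (Class B2/C subsidized wards as reference case), average daily bed cost, total OT/PT sessions".

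Section 3.7 takes the difference in mean total cost between groups, divides it by the difference in mean QALYs, and reads the result against SGD 50,000–100,000 per QALY. Section 3.9 lists deterministic sensitivity analyses on equipment cost, therapist time cost, discount rate and utility mapping.

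**The concern.** From a healthcare-system viewpoint, the quantity of interest is what the system spends on the resources used. A billed charge is a price, and it need not equal that cost. The gap may be wide where the reference case is a subsidized ward, because a bill net of subsidy omits money that the system still pays, and a bill gross of subsidy may carry a margin. The article does not say which kind of bill is meant.

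This matters because the ICER numerator adds two kinds of component. The BCI add-on enters at institutional cost. Any saving or extra use in bed days, outpatient care or readmissions enters at charges. If the two price levels differ, the trade-off between the add-on and its offsets is weighted wrongly. The scenario in section 3.9 that looks for the minimum substitution level giving a favorable ICER would carry the same error. A larger sample would not remove it.

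**Working it through.** The article gives no cost figure, so there is none to reproduce. The check is algebra on the stated rule, followed by an illustration.

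**Inputs from the article.** Routine healthcare is at billed charges where available and unbilled BCI items are at institutional cost (section 3.5). Routine utilization counts in both groups and BCI items in one (Table 2). The ICER numerator is the difference in mean costs (section 3.7). There are up to 15 sessions (section 2.6), each with 30 min of BCI plus 60 min of standard OT, against 60 min of OT in standard care (section 3.5).

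**Inputs that are assumptions.** The charge-to-cost ratio r is taken from 0.2 to 1.5. It is treated as one number for all routine items and as equal in both groups. The utilization difference dU is taken from −150 to +100 per 100 units of add-on cost.

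**Step 1: the increment.** Let U_B and U_C be mean routine use at cost in the BCI and control groups, with dU = U_B − U_C.

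- One cost basis: (I + U_B) − U_C = I + dU.
- Rule in section 3.5: (I + r·U_B) − r·U_C = I + r·dU.
- Error: (r − 1)·dU. It is zero if r = 1 or dU = 0.

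**Step 2: illustration with I = 100.**

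| dU | One cost basis | r = 0.2 | r = 0.5 | r = 1.5 |
|---|---|---|---|---|
| −150 | −50 | 70 | 25 | −125 |
| −100 | 0 | 80 | 50 | −50 |
| −50 | 50 | 90 | 75 | 25 |
| 0 | 100 | 100 | 100 | 100 |
| +50 | 150 | 110 | 125 | 175 |
| +100 | 200 | 120 | 150 | 250 |

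Both the size and the sign of the increment can change. With r below 1, savings and extra use are both understated. With r above 1, both are overstated.

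**Step 3: one resource at two prices.** Over 15 sessions a BCI participant has 15 × 60 min = 15 h of standard OT and 15 × 30 min = 7.5 h of extra therapist time. The rule prices the first at charges where available and the second at institutional cost. On one basis the extra time is 7.5 / 22.5 = 33% of OT cost. On the mixed basis it is 7.5 / (7.5 + 15r): 71% at r = 0.2, 50% at r = 0.5 and 25% at r = 1.5. This affects the reported make-up of cost. It does not change the increment if both groups receive the same standard OT.

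**Step 4: scale against the threshold (illustrative only).** Assume a utility gain of 0.05 held for 24 weeks: 0.05 × 24/52 = 0.0231 QALY. For each SGD 1,000 of true difference in routine use, the error is SGD 800 at r = 0.2, and SGD 500 at r = 0.5 or, in the opposite direction, at r = 1.5. Divided by 0.0231, that shifts the ICER by about SGD 34,700 or SGD 21,700 per QALY.

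**The case against.** The strongest reply is that Table 2 applies utilization costs to both groups. A reader might infer from section 3.5 that standard care is priced at charges and the BCI group at cost. The article does not support that. A BCI participant's bed days, therapy and readmissions follow the same rule as a control's, so equal use cancels. The split is by cost component, not by arm. This part of the reply stands, with one condition: the words on availability do not guarantee that the same basis is used for every item or patient.

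A reader might also infer that the article contradicts itself on the price source. Section 3.3 draws control inpatient costs from administrative and costing databases, but these are the same two sources that section 3.5 names. The average daily bed cost in Table 2 names a component and sets no clear rival rule. Nor does the article show that ward-class differences between groups would leak into the result: the B2/C reference case seems meant to standardize ward class, although how it combines with actual bills is unclear.

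A third tempting inference is that the rule understates offsets. That holds only if charges lie below cost, which the article does not establish.

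It is also fair that the analysis is labelled exploratory, that the valuation is openly called pragmatic, and that a condensed article may leave the handling of subsidy to a fuller document. The point rests on the charges-first order that is stated, not on that silence. Varying equipment and therapist-time costs (section 3.9), and reporting therapist time apart from device cost (section 2.6, Concomitant Therapy), limit the harm. Neither puts the components on one basis.

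**Conclusion.** The concern holds by cost component. Followed as written, section 3.5 gives an incremental cost of I + r·dU where the healthcare-system perspective calls for I + dU, and no planned analysis varies the price basis. The distortion needs two conditions: routine use must differ between groups, and charges must differ from costs. Its direction is not determined by the article.

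No magnitude can be claimed, because the article gives no r, no expected utilization difference and no expected QALY gain. The figures above show only that, under the assumed ranges, the sign of the increment can change and the ICER can move by an amount that is not small beside the SGD 50,000 threshold. To say that the ICER could not be read against a threshold at all would go too far. The exploratory status keeps this below a critical fault, but the estimates are meant to inform resource allocation (section 4), so the rule should be corrected.

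**What to change.** In section 3.5, replace the charges-first rule for the base case. Apply one set of 2025 institutional unit costs, gross of subsidy, to measured resource use (bed days, therapy minutes, visits, readmissions) in both groups and to the BCI add-on. Price an hour of therapist time the same whether it is standard OT or added BCI time. Sections 3.3 and 3.5 already name an institutional costing source. Nothing in the article shows that it covers community therapy, outpatient visits or all readmissions, so use standard unit costs for items it does not cover.

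In section 3.9, add an analysis that values routine care at billed charges, stated as gross or net of subsidy.

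The cost is a wording change, a data request to the costing source and a short search for unit costs outside it. The downside is that the base case loses some patient-level billing detail, which the sensitivity analysis keeps.
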